## Abstract

This protocol outlines a prospective study aimed at enhancing the diagnosis and monitoring of brain tumors through advanced non-invasive imaging techniques. While magnetic resonance imaging (MRI) is a cornerstone of brain tumor diagnostics, it often lacks the specificity required for definitive diagnosis, which typically relies on invasive tissue sampling. To address this, the study will evaluate advanced MRI techniques—such as perfusion, diffusion, blood-oxygen-level-dependent imaging, magnetic resonance spectroscopy, and amide proton transfer-weighted imaging— that offer valuable physiological and molecular insights, beyond conventional anatomical imaging. Despite their potential, clinical adoption of these methods remains limited. MRI also plays a central role in treatment response assessment and follow-up, yet conventional anatomical sequences may not detect early physiological changes or differentiate true progression from pseudoprogression. Advanced imaging methods have shown promise in addressing these limitations, and predictive models for recurrence risk could further personalize treatment strategies. In this study, imaging will be performed using a standardized 3T MRI scanner at multiple time points: preoperatively, before radiotherapy, during treatment, and throughout follow-up. This protocol aims to establish a multiparametric imaging framework capable of capturing dynamic physiological and molecular changes in brain tumors. The primary goal is to determine whether combining advanced sequences improves diagnostic accuracy compared to conventional MRI, using histopathology as the reference. Secondary objectives include predicting treatment response, distinguishing true progression from pseudoprogression, and modeling spatial recurrence risk based on quantitative imaging biomarkers. We hypothesize that a multiparametric imaging approach will, enable earlier detection of tumor progression and support more precise, individualized treatment decisions.

## Introduction

Diagnostics and characterization of brain tumors are done on the basis of either magnetic resonance imaging (MRI) or a sample taken from the tumor [1]. In majority of cases, MRI cannot give the exact diagnosis, and an accurate histological diagnosis can only be determined from the tissue sample. Obtaining invasive tumor samples either with biopsy or in open surgery has notable risks [2]. Hence, there is a need for a reliable, non-invasive detection method to identify brain tumor types and malignancies safely.

The treatment plan is usually made based on the diagnosis obtained from the MRI and tissue samples. Thus, accurate diagnosis is crucial for patients’ further treatment. Treatment strategies vary depending on the tumor type, grading, patient age, clinical condition, including functional level, and molecular characteristics of the tumor [3,4]. In most cases, surgical resection is the primary treatment option. Radiotherapy is utilized on unreachable targets or as an adjuvant treatment after surgical resection [4]. Chemotherapeutic agents can be combined with radiotherapy or utilized as the main treatment modality in certain cases [5].

To improve tumor diagnostics, more advanced imaging sequences are required. Development of novel MRI devices and sequences has reduced the imaging time significantly, making them more feasible in clinical imaging settings as well. Perfusion imaging can be used to evaluate the tumor grading, as higher-grade tumors have different microvascularity compared to lower grade tumors. Additionally, diffusion imaging and blood-oxygen level dependent (BOLD) imaging have shown potential for tumor grading [6–9] but neither of these are yet widespread in clinical use. Even though these methods can give some information about tumor grading, they are not specific to different tumor subtypes, and they all fail to provide information about the molecular characteristics of the particular tumor.

The molecular content of the tumor can be studied using magnetic resonance spectroscopy (MRS) and chemical exchange saturation transfer (CEST) imaging methods. Among the CEST methods, especially the amide proton transfer weighted (APTw) imaging has shown promising results [10–12]. Both methods, MRS and APTw, provide complementary molecular-level information beyond conventional water proton signals, thereby offering insights that are not attainable with standard MRI techniques. Although these techniques hold promise for enhancing the diagnostic accuracy of brain tumors, their clinical implementation remains limited. This is primarily due to variability in imaging analysis outcomes, which can arise from differences in MRI hardware, magnetic field strengths, and acquisition parameters [13,14].

MRI is also the gold standard in the evaluation of current tumor load and follow-up of treatment response [15–17]. The use of Response Assessment of Neuro-Oncology (RANO) criteria and similar MRI protocols are recommended for accurate and comparable assessment of tumor response [1,18–20]. Current recommendations for follow-up imaging include widely used anatomical MRI sequences that do not provide information on the physiological and biological characteristics of the particular tumor. This may lead to a delay in the recognition and treatment of tumor progression.

Advanced imaging methods may provide additional information on treatment response. For example, perfusion imaging can show changes in oxygen status [21], blood volume [22], and perfusion speed [23] in the treatment area. Diffusion imaging can be used to monitor tissue cellular density and differences in microstructures [24], and BOLD can point out hypoxic zones and changes in functional brain areas. [25]. Post-treatment metabolic changes can be studied with MRS and CEST imaging [24,26]. For example, the overall CEST signal decrement has been found to be an early indicator of treatment response [26,27].

Additionally, it is well known that radiotherapy may induce changes in the tumor, such as necrosis and an inflammatory reaction. These conditions can mimic tumor progression (so-called pseudoprogression) on the conventional clinical MRI sequences, which cannot differentiate real progression from pseudoprogression. A more reliable differentiation would improve patient care significantly since treatment choices in these conditions differ greatly from those of real tumor progression. False interpretation of imaging results can lead to unnecessary surgeries, which always include risks and decrease patients’ quality of life, at least temporarily. Currently, there are no clinically relevant methods to differentiate pseudoprogression from tumor progression, even though several previously introduced MRI sequences have shown evidence of increased accuracy [27–34].

For treatment optimization, it would be valuable to be able to predict the location of increased risk for tumor recurrence and/or progression. Such predictive capability would allow for targeted dose escalation in high-risk areas to prevent progression, while enabling dose de-escalation in regions with a lower likelihood of recurrence, thereby minimizing toxicity. Although some promising methods have been proposed, further research is required to improve the accuracy and clinical applicability of spatial risk prediction models [35–37].

The difficulties in diagnostics and follow-up of the heterogenic continuum of brain tumors with traditional MRI are well known, and many attempts have been made to overcome these. Despite numerous studies exploring individual advanced imaging techniques, most have been limited to one or two modalities and lack integration into routine practice. A comprehensive, multiparametric approach is needed to identify optimal combinations of sequences that can support precise diagnosis and treatment decisions throughout the disease course [21–33]. This single-center protocol addresses these gaps by implementing a standardized multiparametric MRI framework using a consistent 3T scanner and harmonized acquisition parameters. The controlled setting minimizes technical variability and enables high-quality, reproducible data collection. Integration with clinical workflows allows real-time validation against histopathological findings and treatment outcomes.

The study combines multiple advanced imaging modalities in a longitudinal design, capturing tumor dynamics across key treatment phases. This approach enables robust evaluation of diagnostic accuracy, prediction of treatment response, differentiation of true progression from pseudoprogression, and modeling of spatial recurrence risk. The findings are expected to inform future multicenter trials and contribute to the development of clinically applicable imaging biomarkers for personalized neuro-oncology care.

## Materials and methods

This study protocol was developed in accordance with the SPIRIT (Standard Protocol Items: Recommendations for Interventional Trials) guidelines, adapted as appropriate for a non-randomized design [38]. The aim of this study (Fig 1) is to improve the diagnostics and follow-up of brain tumors using advanced non-invasive multi-parametric MR imaging (mpMRI). All adult brain tumor patients undergoing brain surgery, radiotherapy, or chemotherapy treatment in the Oulu University Hospital (OUH) fulfilling study criteria will be asked to participate in the study. All participants will have MR imaging done using the same 3T MAGNETOM Vida (Siemens Healthineers AG, Forchheim, Germany) at every time point during the treatment course. Current clinical MRI sequences will be obtained according to the usual institutional protocol. Additionally, mpMRI will be performed preoperatively, prior to the radiotherapy, and during the follow-up. Follow-up mpMRI will be performed at the same time as clinical imaging follow-up in accordance with patients’ treatment plans. Participants having radiotherapy will also be scanned midway through the radiation treatment course and after its completion. The number of follow-up scans for each participant will depend on their treatment plans; glioma patients’ follow-up will continue as long as the study is ongoing, and other brain tumors will have at least one one-year follow-up scan after the treatment if no further treatments are planned.

**Fig 1 pone.0336387.g001:**
[figure not shown]
Main objectives of the study: Radiological assessment is integrated throughout the treatment timeline—starting with the preoperative phase, where imaging is used to predict underlying pathology; continuing through oncological treatment, where therapeutic response is evaluated; and extending into the follow-up phase, where imaging aids in assessing and predicting disease progression, including the differentiation of true progression from pseudoprogression. Figure created with BioRender.com (license to publish obtained).

The study began at the end of 2022 following approval by the Ethical Committee of the Northern Ostrobothnia Hospital District. Patient recruitment and data collection are an ongoing process, initially started on March 23, 2023. These phases are expected to be completed by the end of 2027, as the ethical approval remains valid until October 10, 2027. However, if the number of participants is below expectations, amendments to the research protocol and ethical approvals will be submitted to extend the timeframe for participant recruitment. We aim to recruit 50–70 new patients annually, representing approximately 30–50% of those meeting the inclusion criteria each year. This recruitment target has proven feasible: at the time of manuscript submission, 104 patients have been successfully enrolled, yielding a total of 221 individual imaging sessions. We aim to recruit 50 participants representing major brain tumor subtypes—including glioblastoma, low-grade glioma, and meningioma. This sample size is notably larger than the median (~25) typically reported in neuroimaging studies, enabling robust and reliable subgroup analyses [39]. The final results of the study are expected to be available by the end of 2028, assuming no extensions to recruitment or data collection are required.

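### The target of 50 participants does not fit the accrual figures unless it means 50 per subtype, and exceeding a typical study size does not establish reliable subgroup analyses

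*Protocol article*

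**What the plan says.** All the size statements stand in one paragraph of the protocol article, under Materials and methods, after the caption of Fig 1.

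- **Accrual goal:** "We aim to recruit 50–70 new patients annually, representing approximately 30–50% of those meeting the inclusion criteria each year".
- **Timing:** recruitment "initially started on March 23, 2023", with recruitment and data collection "expected to be completed by the end of 2027, as the ethical approval remains valid until October 10, 2027".
- **Progress at submission:** "104 patients have been successfully enrolled, yielding a total of 221 individual imaging sessions".
- **Target:** "We aim to recruit 50 participants representing major brain tumor subtypes", with the subtypes described as "including glioblastoma, low-grade glioma, and meningioma".
- **Justification:** "This sample size is notably larger than the median (~25) typically reported in neuroimaging studies, enabling robust and reliable subgroup analyses".

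The paragraph does not say whether 50 is a study total or a number for each subtype, and the article gives no other overall target. The Abstract sets the primary goal as better diagnostic accuracy than conventional MRI, judged against histopathology. The section on data and statistical analyses plans accuracy analyses within tumour subgroups.

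**The concern.** Two things look wrong. First, a target of 50 follows directly on a report of 104 enrolled and an annual goal that reaches 50 within a year, so the number taken literally cannot be the study's size. Second, the article attaches a property to the 50, namely that subgroup results will be dependable. The only ground offered is that 50 is larger than a typical neuroimaging sample. That is a comparison with other studies' habits. It does not state the precision or power available for any comparison planned here.

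Readers will use this sentence to judge every subgroup result. If the count is ambiguous, they cannot tell whether a subgroup was meant to hold about 17 patients or 50. If the reliability claim is taken at face value, a null or imprecise within-subtype accuracy comparison may be read as more informative than it is.

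**Working it through.** **Can the 50 be reproduced?** No. The article gives no significance level, power, effect size or precision target from which to derive it. It can only be checked against the neighbouring figures and against assumed inputs.

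**Step 1: the target against accrual.**
- 23 March 2023 to 10 October 2027 is 1,662 days, and 1,662 / 365.25 = 4.55 years.
- Implied enrolment: 4.55 × 50 = 228 (rounded) to 4.55 × 70 = 319 (rounded). To the end of 2027 (4.77 years) it is 239–334.
- 104 / 50 = 2.1, so a total of 50 had been passed twice over at submission.

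**Step 2: 50 as a total.** 50 / 3 = 16.7, or about 17 per named subtype. An equal split is an assumption, and the list of subtypes is open-ended, so the average could be lower. Seventeen is below the article's own benchmark of about 25.

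**Step 3: 50 per subtype.** 3 × 50 = 150 for the three named subtypes, which is below 228. No figure conflicts, although the article does not give the mix of subtypes.

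**Step 4: precision with 50 in a subtype.** Clopper-Pearson 95% limits for x successes in n are the 2.5% quantile of Beta(x, n−x+1) and the 97.5% quantile of Beta(x+1, n−x). The observed sensitivity of 80% is assumed.
- 40/50: 0.663 to 0.900, a half-width of (0.900 − 0.663)/2 = 0.118, or about 12 points.
- For comparison, 14/17 (82%): 0.566 to 0.962. This applies only if 50 is the total and is split equally.

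**Step 5: paired accuracy within one subtype of 50.** Assume each patient is classified by both mpMRI and conventional MRI. Let D be the proportion of patients on whom exactly one method is correct, and d the gain in accuracy. Then p10 = (D + d)/2 and p01 = (D − d)/2. The number of discordant pairs m is Binomial(50, D), and the number favouring mpMRI given m is Binomial(m, p10/D). Power is the probability that the exact two-sided 5% McNemar test rejects in favour of mpMRI, summed over m. D of 20–30% is an assumption.

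| Gain d | Power, D = 20% | Power, D = 30% |
|---|---|---|
| 10 points | 24% | 18% |
| 15 points | 59% | 41% |
| 20 points | 95% | 70% |

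The 95% entry is a limiting case: with d = D, every discordant pair favours mpMRI. Solving for 80% power gives a detectable gain of about 18 points at D = 20%, 20 points at D = 25% and 22 points at D = 30%.

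**Step 6: comparisons where the numbers do better.**
- Two subtypes of 50 each, two-sided 5%: power is about 98% for a standardised mean difference of 0.8 and about 70% for 0.5. The difference detectable with 80% power is (1.96 + 0.84) × √(2/50) = 0.56.
- All subtypes pooled, same exact McNemar test, gain of 10 points: 92% (n = 228) to 98% (n = 319) at D = 20%, and 76% to 89% at D = 30%. For 15 points it is about 99% or more throughout. These figures assume that every enrolled patient has usable paired images and histology.

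**The case against.** The strongest reply is that nobody would read 50 as the total when 104 enrolled patients are reported one sentence earlier. The sentence lists subtypes, the next speaks of subgroups, and the comparison with a median of about 25 makes sense only for a group of 50. On that reading at least 150 patients are needed, the accrual covers them, and the defect is a missing phrase. This largely stands: the numerical conflict is conditional on 50 being the total, and the figures for 17 patients belong to that less plausible reading only. What remains is that the text does not say what the 50 counts.

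A reader might also infer that the design fails to deliver reliable subgroup analyses on either reading. The document does not support that. It names no effect size, discordance or precision target, so failure with 50 per subtype cannot be proved. Fifty per group also does well for large differences between subtypes, and group-level comparisons across tumour types are planned. Nor is the primary goal shown to be underpowered. The Abstract does not confine it to one subtype, and the pooled comparison is much stronger than the within-subtype one.

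Finally, a reader might extend the argument to pseudoprogression and recurrence, supposing that these rest on a small part of one subtype. The article nowhere restricts those analyses in that way, so no figure is offered for them.

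The objection does not rescue the justification. This is no complaint that a power calculation was left to a fuller document. The article makes a positive claim about reliability, and the reason given does not carry it.

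**Conclusion.** The point holds in a limited form and should be fixed. As a study total, 50 is irreconcilable with 104 enrolled and with the 228–319 implied by the annual goal. As 50 per subtype, the likelier intent, the numbers fit but the wording leaves it unsaid. On neither reading does exceeding a median of about 25 establish dependable subgroup analyses.

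For the within-subtype accuracy question, 50 patients give roughly ±12 points at 80% sensitivity and 80% power only for paired gains of about 18–22 points. Gains of 10–15 points would usually be missed, except that power reaches 59% at 15 points with 20% discordance. These sizes rest on an assumed sensitivity of 80%, assumed discordance of 20–30%, a paired exact test at the two-sided 5% level, and all 50 patients analysable. The article excludes scans with severe artefacts without giving a rate, and any such loss would lower the figures. The finding concerns the stated number and the claim attached to it; it does not show that the study is too small for its purpose.

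**What to change.** Three changes to the recruitment paragraph:

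1. State whether 50 is per subtype. If so, say that the three named subtypes need at least 150, and set this beside the 104 enrolled and the 228–319 expected by 10 October 2027 at the stated annual rate. If something else is meant, say what, and reconcile it with the same figures.
2. Replace the reliability claim with what 50 patients give: a 95% interval of about ±12 points around a sensitivity of 80%.
3. Add the within-subtype paired difference detectable with 80% power, roughly 18–22 points, and state the assumed discordance of 20–30%. The authors may fairly add that between-subtype and pooled comparisons do better.

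The cost is a text correction. Enrolment, imaging and analysis do not change. The one downside is that the stated reliability of the subgroup results will look less favourable.

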### MRI sequences

MpMRI studies are conducted with a 64-channel phased-array head coil. Anatomical isotropic 3D T1 and T2-weighted sequences are imaged with resolution ≤ 1 mm^3^ and Dotarem® (Gd-DOTA; Guerbet, Villepinte, France) is used for contrast enhancement when clinical imaging is performed at the same time. Diffusion tensor imaging (DTI) is imaged with 64 directions and b-values of 0 and 1000. If the patient has trouble staying still, the number of directions will be dropped to 20. For 5-minute resting state BOLD imaging, echo planar imaging technique is used, and 300 volumes are collected. Participants are instructed to lay still with their eyes open and not to think about anything particular. MRS is imaged with intermediate echo time (TE = 135ms) in three directions (3D) always when possible due to the anatomical location of the tumor. 3D MRS is planned with either a T1- or T2-weighted image, depending on the visualization of the tumor. If acquiring 3D MRS is not possible, then 2D or single voxel spectroscopies are used. In single voxel MRS, one voxel is placed to contain the tumor, and other is placed contralateral to the tumor containing healthy brain tissue for comparison. Amide proton transfer weighted (APTw) CEST sequence is scanned with 20 volumes and phases from −4.5 ppm to +4.5 ppm with 0.5 ppm intervals. For perfusion imaging, we utilize pseudo-continuous arterial spin labeling (pCASL) with a labeling duration of 1800 ms and a multi-inversion time technique. The time-of-flight sequence is used for planning the pCASL sequence. Dynamic susceptibility contrast MRI (DSC-MRI) is also performed, when contrast enhancement is used.

### Inclusion criteria

Age ≥ 18Suspected brain tumor undergoing brain surgery, radiotherapy, or chemotherapy treatment at Oulu University HospitalThe patient tolerates repeat MRI scans without sedation

### Exclusion criteria

Age < 18Previous brain tumor treatments3T MRI contraindicated (e.g., metallic implants, cochlear implants, neurostimulators)The patient is unable to provide informed consent

### Workflow

The complete workflow of this protocol is illustrated in Fig 2. Once a patient is deemed eligible for the study, the research nurse will seek for oral and written informed consent from the patient for their participation. If the patient agrees to participate, the research nurse schedules an additional mpMRI to be performed alongside the clinically indicated MRI using the 3T MAGNETOM Vida scanner. All study personnel have received training from a medical physicist specialized in MRI, who also provides on-site support during each imaging session. All participants are imaged before the planned treatment. During the surgery, the location from which the sample is taken is either documented using a navigator screenshot or by the surgeon describing the location in the patient’s chart (in the referral letter of the sample for pathology). Radiotherapy planning-related data, including tumor/treatment target and organs at risk contours, simulated radiation dose distributions, and treatment plans, are saved for further evaluation. MpMRI is done before the radiotherapy, midway through the treatment course, and after the last treatment fraction (preferably on the same day). Other follow-up imaging is performed according to the particular patient’s clinical follow-up plan, and at least one one-year follow-up imaging after treatment is taken.

